# The Symptom Monitoring with Feedback Trial (SWIFT): protocol for a registry-based cluster randomised controlled trial in haemodialysis

**DOI:** 10.1186/s13063-022-06355-0

**Published:** 2022-05-19

**Keywords:** Kidney replacement therapy, Renal dialysis, Haemodialysis, Patient-reported outcomes, Chronic kidney disease, Quality of life, Registry, Cluster and randomised controlled trial

## Abstract

**Background:**

Kidney failure prevalence is increasing worldwide. Haemodialysis, peritoneal dialysis or kidney transplantation are undertaken to extend life with kidney failure. People receiving haemodialysis commonly experience fatigue, pain, nausea, cramping, itching, sleeping difficulties, anxiety and depression. This symptom burden contributes to poor health-related quality of life (QOL) and is a major reason for treatment withdrawal and death. The Symptom monitoring WIth Feedback Trial (SWIFT) will test the hypothesis that regular symptom monitoring with feedback to people receiving haemodialysis and their treating clinical team can improve QOL.

**Methods:**

We are conducting an Australia and New Zealand Dialysis and Transplant (ANZDATA) registry-based cluster randomised controlled trial to determine the clinical- and cost-effectiveness at 12 months, of 3-monthly symptom monitoring using the Integrated Palliative Outcome Scale-Renal (IPOS-Renal) survey with clinician feedback, compared with usual care among adults treated with haemodialysis. Participants complete symptom scoring using a tablet, which are provided to participants and to clinicians. The trial aims to recruit 143 satellite haemodialysis centres, (up to 2400 participants). The primary outcome is change in health-related QOL, as measured by EuroQol 5-Dimension, 5-Level (EQ-5D-5L) instrument. Secondary outcomes include overall survival, symptom severity (including haemodialysis-associated fatigue), healthcare utilisation and cost-effectiveness.

**Discussion:**

SWIFT is the first registry-based trial in the Australian haemodialysis population to investigate whether regular symptom monitoring with feedback to participants and clinicians improves QOL. SWIFT is embedded in the ANZDATA Registry facilitating pragmatic recruitment from public and private dialysis clinics, throughout Australia. SWIFT will inform future collection, storage and reporting of patient-reported outcome measures (PROMs) within a clinical quality registry. As the first trial to rigorously estimate the efficacy and cost-effectiveness of routine PROMs collection and reporting in haemodialysis units, SWIFT will provide invaluable information to health services, clinicians and researchers working to improve the lives of those with kidney failure.

**Trial registration:**

Australian New Zealand Clinical Trials Registry ACTRN12620001061921. Registered on 16 October 2020

**Supplementary Information:**

The online version contains supplementary material available at 10.1186/s13063-022-06355-0.

## Administrative information

Note: the numbers in curly brackets in this protocol refer to SPIRIT checklist item numbers. The order of the items has been modified to group similar items (see http://www.equator-network.org/reporting-guidelines/spirit-2727-statement-defining-standard-protocol-items-for-clinical-trials/).

## Introduction

### Background and rationale {6a}

Kidney disease, consisting of chronic kidney disease (CKD), acute kidney injury (AKI) and kidney failure, affects 850 million people globally [1–3]. People with kidney failure can receive kidney replacement therapy (KRT) in the form of either dialysis or kidney transplantation to extend life. It is predicted that by the year 2030, the need for KRT will reach approximately 5.4 million people, the majority in low- and middle-income countries [4]. Dialysis, the most common KRT worldwide, has significant costs yet results in only 51% survival at 5 years [5], lower than all cancers combined [6]. In Australia in 2020, 13,931 people were receiving dialysis; 10,470 (75%) in haemodialysis facilities (non-hospital or hospital) with 9% undertaking haemodialysis at home and a further 16% performing peritoneal dialysis [7].

Facility-based haemodialysis typically requires three treatment sessions per week for 3 to 5 h per session. This treatment removes solutes and fluid directly from the blood; however, people receiving this therapy frequently report symptoms of fatigue, pain, nausea, cramping, hypotension, itching, sleeping difficulties, anxiety and depression [8]. This is reflected in the low quality of life (QOL) of people receiving facility-based haemodialysis, with self-reported QOL at 59% of full health [9]. This is lower than the self-reported QOL of people with metastatic prostate cancer or spinal cord injury [10].

Overwhelming symptoms and poor QOL can lead to dialysis withdrawal and death. In 2020, the ANZDATA Registry reported 575 deaths (34% of all haemodialysis deaths) attributed to withdrawal of haemodialysis [11]. Of these, 202 (35%) were due to psychosocial reasons, including symptom burden and poor QOL [11]. More frequent or longer dialysis sessions may reduce some symptoms; however, this strategy may only result in small improvements in QOL [12]. Symptom management improves QOL and survival in other disease conditions. In cancer care, symptom monitoring during routine chemotherapy improved survival compared with usual care [13]. Symptom management in palliative care improved QOL, reduced symptoms and increased functional wellbeing compared with standard care [14]. The use of patient-reported outcome measures (PROMs) including symptom monitoring is recommended to guide clinical care for many conditions; however, few trials have assessed the effectiveness of this intervention [1]. In haemodialysis populations, although effective targeted management of symptoms is associated with improved QOL [15], evidence is lacking from randomised controlled trials (RCT).

In 2020, we completed a SWIFT pilot study among four dialysis units in South Australia and Queensland [16, 17]. Both patients and clinicians found the tablet computers easy to use and felt that electronic collection of PROMs was useful and important for patients’ QOL. The pilot concluded that electronic symptom monitoring in adults on haemodialysis with feedback to clinicians was feasible [17]. Lessons learned from the pilot have shaped the design of the main trial.

### Objectives {7}

SWIFT evaluates the hypothesis that regular symptom monitoring with feedback to people receiving haemodialysis and their clinicians improves QOL at 12 months. SWIFT is a registry-based cluster RCT to determine the clinical- and cost-effectiveness of 3-monthly symptom monitoring using the validated Integrated Palliative Outcome Scale – Renal (IPOS-Renal) survey. The intervention includes symptom score feedback to adult haemodialysis participants and clinicians with links to evidence-based symptom management also sent to clinicians. Secondary outcomes include survival, frequency and severity of symptoms (including haemodialysis-associated fatigue), biochemical measures of dialysis adequacy, dialysis duration and frequency, dialysis withdrawal and healthcare utilisation. In addition, the trial is investigating whether electronic capture of patient-reported outcomes within a clinical quality registry at a national level is feasible and cost-effective.

### Trial design {8}

The trial is a prospective registry-based cluster randomised controlled trial of 3-monthly electronic symptom collection using IPOS-Renal with feedback to clinicians and participants versus usual care for adults managed with centre haemodialysis (Fig. 1). This trial followed the Standard Protocol Items: Recommendations for Interventional Trials (SPIRIT) guideline [18] (see Supplementary Material). Haemodialysis centres (the clusters) will be randomised in a 1:1 ratio with linked parent/satellite centres forced to the same allocated intervention to account for patient movement between centres. The trial will be conducted and reported according to the CONSORT 2010 checklist for reporting a cluster randomised trial [15] and patient-reported outcomes in trials [16]. The CHEERS guidelines will guide reporting of cost-effectiveness [19].

**Fig. 1 Fig1:**
[figure not shown]
Trial schema for SWIFT

## Methods: participants, interventions and outcomes

### Study setting {9}

SWIFT is being conducted in both public and private haemodialysis centres across Australia. These are centres that are predominantly nurse-managed with visiting on-site physician attendance [20]. Haemodialysis is covered by publicly funded healthcare coverage and is primarily provided by state-run health networks. Some networks have contracted private providers for some or all satellite dialysis services. Regardless of provider, all dialysis care is free to the patient [21], and all dialysis units send patient data to the ANZDATA Registry.

### Eligibility criteria {10}

#### Inclusion criteria

All centres contributing to the ANZDATA Registry (a bi-national registry which covers all chronic dialysis providers) with a minimum of 10 patients are eligible for participation. Within these centres, adults aged 18 years and older, who are willing and able to adhere to all trial requirements and able to provide informed consent, will be invited to participate. In order to encourage participation of those from a culturally and linguistically diverse background, SWIFT has translated survey materials for adults who read simplified Chinese, traditional Chinese, Vietnamese, Korean, Arabic, Greek or Italian text. Centres currently using the IPOS-Renal questionnaire for symptom assessment are still eligible to participate if they agree to use the tablet-based SWIFT data collection and follow the protocol as per their allocation during the trial period.

#### Exclusion criteria

People under 18 years of age or unable to provide informed consent are excluded. In addition, those people or centres who are participating in programmes or trials in which an extensive electronic symptom monitoring and feedback management system is already in place (where the centre or individual is not willing to pause current management, and where co-enrolment is unfeasible) are excluded.

### Who will take informed consent? {26a}

The nurse champion or their delegate (other nursing staff, allied health professionals, clinical research assistants or other nominated persons) in each dialysis centre will assist with recruitment and consent by distributing the patient information sheets prior to survey completion and are available to answer trial-related questions from participants. The nurse champion takes responsibility for conducting the trial in their unit and is responsible for leading participant recruitment. Consent is obtained electronically from each participant prior to commencing the baseline survey.

### Additional consent provisions for collection and use of participant data and biological specimens {26b}

Additional consent will be sought from Australian participants for access to their hospitalisations and Medicare Benefits Schedule (MBS) and Pharmaceutical Benefits Scheme (PBS) records through registry data linkage. No biological specimens will be collected.

### Interventions

#### Explanation for the choice of comparators {6b}

As SWIFT is a pragmatic trial, usual care in the dialysis unit (the control arm) is the comparison to symptom monitoring and feedback. Participants in the control arm will not complete electronic 3-monthly IPOS-Renal measures, and the participants and clinicians in the control arm will not receive symptom scores with evidence-based recommendations for their management. Both arms will collect health-related quality of life through the EQ-5D-5L instrument, and these scores will not be fed back to clinicians or participants. Usual care will consist of the dialysis centre’s standard practice for measuring or monitoring symptoms and may constitute no symptom monitoring, ad hoc monitoring and monitoring using other mechanisms, (e.g. questions in a nursing assessment when a dialysis session is commenced, or medical history within a nephrology consultation). The ANZDATA audit of PROMs in haemodialysis centres revealed only around 12% of centres used symptom measures in a routine and systematic way during haemodialysis care [17, 22].

#### Intervention description {11a}

The intervention comprises regular measurement of symptom burden with feedback of these results to participants and clinicians. Participants in the intervention arm will complete the IPOS-Renal at baseline, 3 months, 6 months, 9 months and 12 months, within a 2-week window (Table 1). The individual participant’s IPOS-Renal results will be emailed to the centre nurse unit manager or delegate, and the participant’s treating nephrologist. Within the email will be a link to evidence-based guidelines for symptom management. The evidence-based guidelines were created by SWIFT Investigators (RLM and AKV) and are updated regularly (SWIFT Investigator BS) to ensure new evidence is incorporated. Any symptom score of 3 (severe symptoms) or 4 (overwhelming symptoms) on a scale of 0–4, on the IPOS-Renal instrument will be flagged for prompting clinical review. All subsequent medical treatments are at the discretion of the treating clinicians. Participants receive a copy of the completed survey emailed to them in real-time if they provide an email address at commencement of the survey. Based on our previous work, we anticipate about 30–40% of participants will provide an email address [17]. If a participant does not have their own email address, they can nominate the address of a family member or close friend. Participants do not receive the evidence-based guidelines for symptom management.

**Table 1 Tab1:** Study timeline schedule

	Patient screening	Baseline	3 months	6 months	9 months	12 months
Patient demographics	X					
Informed consent		X				
EQ-5D-5L questionnaire		X		X		X
SONG-HD Fatigue questionnaire		X		X		X
IPOS Renal (*intervention arm only*)		X	X	X	X	X
Validity questions (all participants)		X		X		X
ANZDATA clinical treatment record	X	X	X	X	X	X
MBS and PBS data						X

*Abbreviations: EQ-5D-5L*, EuroQoL 5-item 5-level preference-based measure of health status, *IPOS Renal*, Integrated Palliative Outcome Scale – Renal, *SONG-HD Fatigue*, Standardised Outcomes in Nephrology – Haemodialysis, Fatigue

The IPOS-Renal is a 15-symptom checklist measures self-reported pain, shortness of breath, weakness, nausea, vomiting, poor appetite, constipation, sore mouth, drowsiness, poor mobility, itching, difficulty sleeping, restless legs, skin changes and diarrhoea. All symptom scores are reported on a 0 to 4 scale (0=not at all, 1=slightly, 2=moderately, 3=severely, 4=overwhelmingly bothered) and indicate the effect of the symptom on the respondent over the past week [23]. The IPOS-Renal takes approximately 9 min to complete and is widely used in palliative care [17]. Its use is recommended in the Australia and New Zealand Renal Supportive Care Guidelines [24].

#### Criteria for discontinuing or modifying allocated interventions {11b}

The trial intervention will be permanently discontinued if the participant declines further collection of PROMs, withdraws their consent to participate in the trial or ceases haemodialysis (i.e. receives a kidney transplant; is transferred to peritoneal dialysis, home haemodialysis or to a non-participating haemodialysis centre). Secondary outcomes will continue to be collected in the ANZDATA registry (see Fig. 2) and through linked administrative data unless consent for these data is also withdrawn.

**Fig. 2 Fig2:**
[figure not shown]
How kidney registries could use their capabilities to provide an infrastructure for facilitating large-scale collection of PROMs to support individual patient management and other purposes for multiple stakeholders

#### Strategies to improve adherence to interventions {11c}

The SWIFT ANZDATA staff member will contact the SWIFT delegate in the unit (usually the nurse unit manager or ANZDATA contact) to compare the list of patients in the unit with those listed in the ANZDATA registry such that any discrepancies can be reconciled. This ensures that only patients who are in the unit at the time of recruitment and eligible for the trial are invited to participate. Each centre will appoint their own SWIFT nurse champion and will be assigned a research assistant (RA) from the SWIFT team. The RA will liaise with the SWIFT delegate in the unit during the trial to assist the coordination of the intervention. Where possible, the RA will attend the centre at the beginning of the trial recruitment phase. The RA will assist with logistical aspects such as site Wi-Fi connectivity and tablet functionality. These strategies to maintain engagement were adopted following consumer consultation in the SWIFT pilot study [16].

#### Relevant concomitant care permitted or prohibited during the trial {11d}

There are no restrictions on concomitant patient care during the trial. If a unit currently uses IPOS-Renal in some capacity, then this will be documented (stratification factor). The unit can be allocated to the control arm (symptom monitoring or feedback), and usual care will continue. If the unit is an IPOS-Renal user and is allocated to the intervention arm, SWIFT will request that the unit use the SWIFT monitoring intervention during the trial period. Units will have access to their patients’ IPOS-Renal data through the feedback and can request EQ-5D-5L data once the trial is complete.

#### Provisions for post-trial care {30}

There are no post-trial care requirements.

### Outcomes {12}

The primary outcome of SWIFT is the change in health-related QOL, as measured by EQ-5D-5L and compared between groups (Table 2). We also hypothesise that symptom monitoring and management may reduce overall and cause-specific mortality (including withdrawal from dialysis). In Australia in 2020, 575 of 1667 (34%) of dialysis deaths were due to withdrawal from dialysis. Of these, 202 (35%) of withdrawals were linked to psycho-social reasons [25]. It is anticipated that close monitoring of symptoms, discussions with patients about management of symptoms and therapeutic multi-disciplinary care aimed at reducing symptom burden may specifically reduce deaths due to withdrawal from dialysis. Secondary outcomes are listed in Table 2. Routine collection of secondary end points through the ANZDATA Registry already exists in an “opt-out” framework (#HREC/17/RAH/408).

**Table 2 Tab2:** Table of SWIFT outcomes

Outcome	Description and unit of measure	Data collection timepoint or registry source

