***Secondary outcome***		
Dialysis withdrawal	Number of participants identified as withdrawal from dialysis	12 months—collected through ANZDATA
Health-related quality of life	Mean change in EQ-5D-5L value (utility) from baseline to 6 months	Baseline, 6 months
Health-related quality of life	Mean change in EQ-5D-5L and VAS scores from baseline at 6 months; and from baseline to 12 months	Baseline, 6 months, 12 months
Overall survival	All-cause mortality rates at 12 months	12 months
Cause-specific mortality (including deaths due to dialysis withdrawal)	Cause-specific mortality rates at 12 months for dialysis withdrawal, cardiovascular, cancer, infection and other causes	12 months
Fatigue	Mean change in SONG-HD Fatigue score at 12 months	Baseline, 6 months, 12 months
Symptom severity	Intervention arm only. Measured by change in IPOS-Renal symptom severity scores	Baseline, 3 months, 6 months, 9 months, 12 months
Haemodialysis duration	Average number of hours per treatment	12 months—collected through ANZDATA
Haemodialysis frequency	Number of treatments per week	12 months—collected through ANZDATA
Haemodialysis adequacy	Urea reduction ratio and Kt/V	12 months—collected through ANZDATA
Symptom-related and general healthcare utilisation	Hospitalisations, Medicare Benefits Schedule (MBS), Pharmaceutical Benefits Scheme (PBS) items	Assessed through linked administrative records for admitted patient data and Medicare claims
Cost-effectiveness	Incremental cost per quality-adjusted life year (QALY) gained reported as an incremental cost effectiveness ratio (ICER) or incremental net benefit (INB)	12 months; EQ-5D-5L utilities collected as per primary outcome; healthcare use identified from linked administrative records

*Abbreviations: ANZDATA*, Australia New Zealand Dialysis and Transplant Registry; *EQ-5D-5L*, EuroQoL 5-item 5-level preference-based measure of health status; *VAS*, visual analogue scale; *SONG-HD Fatigue*, Standardised Outcomes in Nephrology – Haemodialysis, Fatigue; *IPOS Renal*, Integrated Palliative Outcome Scale – Renal; *Kt/V*, K=dialyser clearance of urea, t=dialysis time, V=volume of distribution of urea, this is approximately equal to the patient’s total body water

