### Sample size {14}

SWIFT will recruit 143 haemodialysis centres (or clusters) in Australia. Recruitment data from the SWIFT pilot study confirmed the assumptions of over 50% patient participation in each centre, and 80% completion of EQ-5D-5L at 12 months [17]. Sites are grouped into clusters (see 16a) of approximately 2 sites/cluster. Approximately seventy-one clusters in each arm (equating to 2422 total participants) will enable us to identify a clinically significant mean (0.07) 7% increase in health-related quality of life (from 0.59 [59%] to 0.66 [66%]) with 90% power. This minimum clinically important difference was determined through review of EQ-5D-5L studies that showed a change in overall utility of between 0.03 and 0.07 across a range of chronic conditions was associated with meaningful and observable improvements in QOL. This minimum effect of 0.07 was considered feasible and is supported by an observational study in New South Wales (NSW) that demonstrated improvement in EQ-5D-5L utility of 0.11 could be achieved with a focus on symptom management (internal publication). The power calculation is based on a two-sided *t*-test with alpha=0.05 and assumes a modest intra-cluster correlation coefficient of 0.1 and a design effect of 3.5 (to account for clustering, allowing for uneven cluster sizes) creating an effective sample size of 692. We assume a standard deviation (SD) of the change between baseline and 12 months of 0.281. The 7% represents a conservative estimate in effect however one which demonstrates a clinically meaningful improvement in QOL and translates to a societal benefit of 640 quality-adjusted life years (QALYs) per year.

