### Recruitment {15}

Contact details of all potential dialysis centres have been sourced from the ANZDATA registry. Centres are invited via email to complete a pre-trial feasibility survey, exploring existing PROMs use and symptom management strategies. Eligible centres that agree to participate will be randomised. All patients attending that site over a 2-week period are invited to participate in the trial. New patients who may be in their first year of dialysis and who are not yet registered with the ANZDATA registry can be added to the Registry (and trial) before the baseline data collection commences. The ANZDATA Registry operates under an “opt out” model of consent; therefore, if a patient is in a participating centre and chooses not to be a part of the Registry, they are not able to join the trial as secondary outcomes will not be able to be collected for them.

Each patient will be provided with a Participant Information Sheet (PIS) and the opportunity to read the document and ask questions. The PIS was prepared with input from an ANZDATA consumer representative, [name] (SM), and trialled by patients in the Royal Adelaide Hospital haemodialysis unit. Both the PIS and the PIS summary have been translated into the seven language translations used for SWIFT and are presented to patients in the unit. A screening log records any patients who decline participation in SWIFT and representativeness of the included sample will be reported. At the participant’s next dialysis session (at least 2 days later), the participant is asked to complete the online survey(s) specific to their trial allocation (intervention or control). The consent form is embedded into the baseline survey of the trial and will be completed electronically. Participants in both groups will be informed to raise any health concerns with their doctor or nurse.

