### Statistical methods

#### Statistical methods for primary and secondary outcomes {20a}

The primary analysis will compare symptom monitoring with feedback versus usual care to evaluate the effect of this intervention on QOL and secondary outcomes at 12 months. Change in EQ-5D-5L (from baseline) will be evaluated at 12 months using a generalised estimation equation regression model, adjusted for stratification factors and accounting for clustering. Analysis of outcomes will be compared using an intention-to-treat analysis and individual participant data will be used for all analyses. Sensitivity analyses excluding clusters that currently use IPOS-Renal as a part of their usual care and excluding participants actively managed through a kidney supportive care programme will be undertaken.

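### Registry death and withdrawal outcomes appear to be compared only in consenting participants; a supplementary analysis of all registry patients at the randomised centres would be a cheap check on selection

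*Protocol article*

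**What the plan says.** **Order of events.** Trial design {8} sets the unit of allocation: "Haemodialysis centres (the clusters) will be randomised in a 1:1 ratio". Recruitment {15} gives the sequence: "Eligible centres that agree to participate will be randomised. All patients attending that site over a 2-week period are invited to participate in the trial". A nurse champion in the unit leads recruitment (section {26a}). Allocation is concealed only up to the site initiation visit (section {16b}), and section {17a} says that blinding within clusters is not possible. The consent form sits inside a baseline survey that is specific to the arm (section {15}).

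**What the registry holds.** Study setting {9} says "all dialysis units send patient data to the ANZDATA Registry". Outcomes {12} adds "Routine collection of secondary end points through the ANZDATA Registry already exists in an" opt-out framework. Before recruitment, trial staff and the unit "compare the list of patients in the unit with those listed in the ANZDATA registry" (section {11c}).

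**Who is analysed.** The withdrawal row of Table 2 is the "Number of participants identified as withdrawal from dialysis". Section {11b} provides for continued collection of secondary outcomes after a participant stops the intervention, unless consent for those data is withdrawn. Section {15} bars registry opt-outs from the trial because their secondary outcomes could not be obtained. The rows for overall and cause-specific mortality name no population. Section {20a} plans an intention-to-treat comparison and says "individual participant data will be used for all analyses". Sample size {14} assumes "over 50% patient participation in each centre".

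**What is said about decliners.** Section {15} provides a screening log and a report on how representative the included sample is.

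**The concern.** For EQ-5D-5L and fatigue, restriction to participants cannot be avoided, because nobody else completes a survey. Death, withdrawal and the dialysis records are different: the registry collects them whether or not a patient joins the trial. Restricting them to participants replaces a comparison of centres as randomised with a comparison of subsets formed afterwards, under known allocation.

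The protocol itself gives a reason why uptake might differ by arm. The intervention arm has five survey timepoints against three in control (section {18a}), and adds a survey of about 9 minutes to one of about 3 minutes (sections {11a} and {12}). Sicker patients might decline the heavier schedule more often, or motivated staff might recruit them harder. The bias could run in either direction.

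At stake is the hypothesis in Outcomes {12} that the intervention may reduce overall and cause-specific mortality, including deaths from withdrawal. If a difference appears among participants, the analyses described could not separate effect from selection.

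**Working it through.** The protocol states no sample size, power or expected rate for the registry outcomes, so there is no figure of its own to reproduce here. The steps below only set the scale.

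**1. Crude rates from the protocol's 2020 figures** (Introduction {6a} and Outcomes {12})
- Deaths: 1,667 / 13,931 = 12.0%.
- Withdrawal deaths: 575 / 13,931 = 4.1%.
- Psychosocial withdrawals: 202 / 13,931 = 1.45%.

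The denominator is all people on dialysis, including peritoneal and home haemodialysis, so these are not centre-haemodialysis rates. With the 10,470 people in haemodialysis facilities as denominator, the last figure is 202 / 10,470 = 1.9%.

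**2. Patients outside the analysed set**

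| Assumed participation | All centre patients | Outside the trial | Deaths among 2,422 participants | Deaths among all |
|---|---|---|---|---|
| 50% | 2,422 / 0.5 = 4,844 | 2,422 | 290 | 580 |
| 60% | 2,422 / 0.6 = 4,037 | 1,615 | 290 | 483 |
| 70% | 2,422 / 0.7 = 3,460 | 1,038 | 290 | 414 |

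Since the protocol assumes more than 50% participation, half is the upper limit for the share left out.

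**3. Selection with no true effect (assumed values)**

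Take two equal strata with 12-month mortality of 8% and 16%. Uptake is 60% in both strata of the control arm, and 60% (well) and 40% (sicker) in the intervention arm.
- Intervention participants: (0.6 × 8% + 0.4 × 16%) / (0.6 + 0.4) = 11.2%.
- Control participants: (0.6 × 8% + 0.6 × 16%) / (0.6 + 0.6) = 12.0%.
- Difference: 0.8 points; ratio 0.93.
- All patients, either arm: 0.5 × 8% + 0.5 × 16% = 12.0%; difference zero.

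Keep the well stratum at 60% and the sicker intervention stratum at 40%. Letting the sicker stratum carry 1.5 to 2 times the mortality, with 50% to 60% uptake in control, gives ratios of 0.93 to 0.98. If uptake among the sicker is reduced equally in both arms, the ratio is 1.00. Only a difference in selection between arms causes bias.

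**4. Precision and dilution, before clustering**
- Participants, 1,211 per arm: SE = √(2 × 0.1197 × 0.8803 / 1,211) = 1.32 points.
- All patients at 50% participation, 2,422 per arm: SE = 0.93 points.
- If decliners gain nothing, a 1.45-point effect becomes 0.725 points, so the ratio of effect to SE falls from 1.45 / 1.32 = 1.10 to 0.725 / 0.93 = 0.78.

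For an assumed risk ratio of 0.75 and an intra-cluster correlation of 0 to 0.02, power is 0.55 to 0.67 in participants and 0.25 to 0.38 in all patients with the effect halved. It would be 0.75 to 0.93 only if the effect reached the whole unit.

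**The case against.** **The analysis plan is not shown, and supplementary populations often belong there.** This stands in part. An all-patient analysis may exist. The point therefore rests on what the article fixes: the withdrawal row, and the way sections {11b} and {15} tie secondary outcomes to those who joined.

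**A reader might infer that section {20a} expressly confines every analysis to consenting participants.** The text does not support that. In a cluster trial, the phrase about individual participant data may mean only that individual records are analysed instead of cluster summaries. The restriction is explicit for withdrawal alone.

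**The participant analysis is legitimate.** The intervention works through each participant's own survey and the emailed result, so decliners receive none of it. This stands. An all-patient analysis answers a different, diluted question and cannot replace the planned one.

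**Selection is already addressed.** All patients attending over two weeks are invited, decliners are logged and representativeness is reported. That helps readers judge the sample, but a description of decliners does not remove a selection effect from a mortality comparison.

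**The registry population is not perfectly clean either.** This stands. Registry opt-outs are missing, and unregistered first-year patients can be added after the centre is randomised (section {15}). It would be too strong to say that the bias is zero by design.

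**Conclusion.** The point holds as a cheap improvement on secondary outcomes. As written, withdrawal, and by implication the other registry outcomes, would be compared in a subset recruited after randomisation by staff who are not blinded. The outcome data for the remaining patients are routinely collected. Under the stated assumptions the spurious mortality difference is 0.8 points. That is an illustration, not a forecast: it needs uptake among sicker patients to differ between arms by 20 percentage points, and it is smaller than one standard error of the participant comparison.

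Two stronger readings should be resisted. First, selection could be made to mimic the whole 1.45-point reduction from preventing every psychosocial withdrawal, but only with uptake chosen for that purpose; nothing in the protocol predicts it. Second, the smaller standard error in all patients could be taken for a gain in power. It is not one if non-participants do not benefit. The value of the extra analysis lies in largely removing selection by consent.

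The point does not extend to the patient-reported outcomes, nor to hospitalisation, MBS and PBS data, which need additional consent (section {26b}).

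**What to change.** Keep the participant analysis. In Table 2 and section {20a}, or in the analysis plan, pre-specify a supplementary analysis of all-cause mortality, cause-specific mortality and dialysis withdrawal:
- **Population:** all adult registry patients dialysing at the randomised centres in the 2-week recruitment window, defined identically in both arms. State how newly added first-year patients are handled.
- **Analysis:** by the centre's allocation, with the same cluster adjustment as the participant analysis.
- **Interpretation:** read the two estimates together with their confidence intervals, treating the all-patient result as a diluted centre-level effect.
- **Mortality rows:** name the analysis population in Table 2.

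Do not make a claim conditional on the two estimates agreeing in direction. When selection alone is at work, the all-patient difference is centred near zero, so its sign screens out little. With a true 1.45-point effect diluted to 0.725 and an SE of 0.93, the sign would be wrong about 22% of the time before clustering.

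**Cost:** a little extra analysis of data that the registry already collects, and ethics confirmation that opt-out registry records, including those of people who declined the trial, may be used this way. The downsides are dilution by non-participants and some remaining selection from registry opt-outs and newly added patients.
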